## **4. Assessment of Objectives**

### **4.1 Immunogenicity assessments**

#### **4.1.1 Primary non-inferiority outcomes**

The primary outcome is non-inferiority of the proportion of participants in the PP population who seroconvert by Day 28 for the lower dose (i.e. 1000 IU, 500 IU, 250 IU) compared to the full dose. Seroconversion is defined as a  $\geq 4$ -fold rise in neutralizing antibody titre between pre-immunization Day 0 and post-vaccination samples. Any PRNT50 value reported as seronegative (below the Limit of Quantification,  $<1:10$ ) will be converted to LOQ/2. Thus a 4-fold rise for a subject who is  $<1:10$  at baseline, is a titre of 20.

#### **4.1.2 Secondary non-inferiority outcomes**

Geometric mean PRNT50 titre (GMT) on Day 0 and Day 28 will be calculated in the PP population. A test of non-inferiority will be performed for the difference in  $\log_{10}$  GMT from baseline to Day 28 between full-dose and lower dose. Geometric fold increase in PRNT50 titre (GMFI) between Day 0 and Day 28 in the PP population will also be calculated and a similar test of non-inferiority performed. Again, any PRNT50 value reported as below the Limit of Quantification (LOQ) will be converted to a titre of 1:5.

The above non-inferiority assessments of seroconversion, GMT and GMFI at Day 28 will also be assessed in the ITT population, in the subset of the ITT population with pre-existing YF neutralizing antibodies at baseline (ITT FV+), and in the subset of the PP population with no reported history of flavivirus infection (PP FV-).

Lower vaccine doses may change the kinetics of antibody response. The assessment of seroconversion rates, GMT, and GMFI 10 days after vaccination in the ITT population will provide important information in the context of fractional dosing in outbreak response. The three immunogenicity outcomes will also be assessed in 2 years post-vaccination in the ITT population to confirm a lasting effect of full and lower dose vaccination.

Each of the above primary and secondary immunogenicity analyses will be performed in the primary study cohort (A) and replicated in the Children (B) cohort, should the sub-studies proceed.

## 4.2 Safety Assessments

The safety of lower and full dose vaccines will be assessed by recording adverse events (AEs) and serious adverse events (SAEs) occurring in the safety population (i.e., those who are randomized and receive a vaccine). Safety outcomes will be actively monitored at the scheduled visits (2-7), 10 and 28 days post-vaccination. Participants will also be advised to report any reactions that concern them to research staff throughout the study.

Any safety event, regardless of seriousness, will be recorded in the CRF. A detailed clinical description of the event using standardized forms will be provided, including the diagnosis, the date of onset and resolution of episode, and outcome. Each event will be coded using MedDRA dictionary, Version 20.0 System Organ Classes and Preferred Terms. The exact version of the dictionary will be mentioned in the footnote of the respective Listing and/or Table.

Each event will be assessed for the degree of certainty with which it can be attributed to vaccination based on previous reports of similar events after YF vaccination or other similar types of vaccination and the temporal association of the event with vaccination. If there is a reasonable possibility that vaccination contributed to the adverse event, the event will be classified as related to vaccination. If there is no suspicion that the event is related to vaccination (e.g, the event does not follow a reasonable temporal trajectory), it will be classified as unrelated. Any event for which a determination cannot be made will be considered unclassified.

### 4.2.1 Serious Adverse Events

A serious adverse event (SAE) is any untoward medical occurrence that either results in death; is life threatening; requires in-patient or extended hospitalization; results in persistent or significant disability or incapacity, or in a congenital anomaly in participant's offspring; or is a medically important event that may jeopardize the participant or require intervention to avoid one of the above outcomes.

SAEs will be actively monitored in the entire safety population at the Day (2-7), Day 10 and Day 28 post vaccination visits. Participants will be instructed to contact the study team to report any possible SAEs (passive assessment) up until the conclusion of the study. All SAEs will be recorded and followed up to resolution, irrespective of the severity and relationship to vaccination.

In addition to the assessments above, investigators will evaluate whether a SAE is an expected reaction to YF vaccination. A SAE will be considered unexpected if the nature, seriousness, severity, or outcome of the event is not consistent with the vaccine's known effects as described in the medical literature and described by the manufacturer in the product specifications. An unexpected SAE determined to be related to vaccination will be clarified as a Suspected Unexpected Serious Adverse Reaction (SUSAR).

### 4.2.2 Adverse Events

An adverse event (AE) is defined as any untoward medical occurrence in a clinical trial participant to whom a vaccine has been administered; it does not necessarily have a causal relationship with the vaccine/vaccination. An AE can therefore be any unfavorable and unintended sign (including an abnormal laboratory finding), symptom, or disease temporally associated with the use of a medicinal (investigational) product, whether related to the medicinal (investigational) product. AEs include all

events including but not limited to injection-site reactions (pain, induration, and erythema) and systemic events (fever, headache, nausea, allergic reactions).

Adverse events will be followed for the first 28 days post-vaccination. At the Day (2-7), Day10 and day 28 post vaccination visits, participants will be asked to describe local and systemic events occurring since the previous visit. In addition to the nature, outcome, and relatedness, each AE will be graded for severity: mild (Grade 1), moderate (Grade 2), severe (Grade 3), or life-threatening or death (Grade 4; note this category would imply a SAE, which would need additional reporting details).

#### 4.2.3 Immediate post vaccination reactions

Immediate Adverse Events (IAEs) are defined as adverse events occurring within 30 minutes post vaccination with either a full or lower dose. All participants in the Safety population will be observed for 30 minutes after vaccination to monitor for any immediate adverse events. A physician equipped with advanced life support drugs and resuscitation equipment will be available in case of anaphylactic shock. The nature, outcome, relatedness, and severity of each IAE will be recorded.

#### 4.2.4 Other Assessments

Data on age at randomisation, sex, area of residence, prior flavivirus infection, and body temperature will be collected at the initial eligibility screening and vaccination (Day 0). Pregnancy testing will be required of all female participants at the initial visit. Pregnancy at time of enrolment is an exclusion criterion. HIV testing will be required for participation. Any individual found to be HIV-positive will complete a CD4 count to determine their baseline CD4 level for analysis. As noted above, participants with a verified CD4 count over 200 cells/mm^3 within the last 6 months may be enrolled based on this test, but CD4 count must still be quantified at baseline for use in analysis.

## 5. Statistical Methods

All statistical methods will be based on the International Conference on Harmonisation (ICH) E9 document "Statistical Principles for Clinical Trials".

### 5.1 Analysis timepoint

The participants will participate in this study to a maximum of two years. The primary endpoint will be assessed 28 days post-vaccination. The two-year visit will mark the end of the study for most participants.

#### 5.1.1 Primary Analysis Time Point, Interim Analysis and Data Monitoring Committee

The primary analysis time point for each study cohort is 28 days post-vaccination, at which point non-inferiority of seroconversion will be assessed among those vaccinated with a lower vaccine dose compared to those vaccinated with a full dose in each study cohort.

One formal statistical interim analysis is planned on the primary outcome (or endpoint) at the primary analysis time point for review by the DSMB. This will utilize immunogenicity data at Day 0 and Day 28, and safety data collected within 28 days of vaccination for AEFIs and throughout the study for SAEs.

The DSMB will assess non-inferiority in seroconversion among adults (cohort (A) at the primary analysis time point before beginning sub-studies of lower dosing in cohort (B) children 9 months to 5 years of age. Children are potentially at higher risk of an adverse event or lower neutralizing titres (and therefore decreased protection against disease) following vaccination with a lower dose. Therefore, it is important to assess immunogenicity and safety in the primary analysis population before beginning these sub-studies. No adjustment for multiple comparisons will be made as only a single confidence interval will be constructed for each lower dose vaccine at Day 28. The DSMB will also assess safety endpoints and select secondary outcomes.

#### 5.1.2 Qualitative Data Analysis

Analysis of qualitative data will follow the framework approach. To ensure that interpretations of quotes are consistent, and that data quality is rigorous and transparent, independent qualitative researchers will code the data; differences between coding will be resolved by group discussion involving other members of the research team. Recurring issues, concepts and patterns will be identified using ground theory and grouped according to thematic areas.

### 5.2 Methods for Handling Missing Data

The numbers (with reasons) of losses to follow-up (dropouts and withdrawals) over the course of the trial will be reported by trial arm. Valid inferences will be made under the missing at random assumption. No imputation will be done in any way.

### 5.3 Statistical Analysis and Tests

Categorical data will be summarised by numbers and percentages. Continuous data will be summarised by mean, standard deviation (SD), and range if data are normally distributed and median, interquartile range (IQR) and range if data are skewed. Minimum and maximum values will also be presented for continuous data. Data will be summarised for each study cohort and each study arm (full or lower dose). All applicable statistical tests will be performed using a 5% significance level. All confidence intervals presented will be 95%.

#### 5.3.1 Baseline Characteristics

Information for each of the following categories will be presented for the adult study and the children sub-study:

- number of individuals screened;
- the number and reason of screen-outs;
- proportion of eligible individuals who consent and are randomized;
- the proportion of randomized individuals vaccinated;
- the proportion of randomized to viremia follow up per day (2-7);
- the proportion of vaccinated individuals who complete a day 10 post-vaccination visit;
- the proportion of vaccinated individuals who complete a day 28 visit;
- the proportion of vaccinated individuals who complete the final analysis period (defined as completing all study activities up to 12 months for the children sub-study, and up to 24 months for the adult study);
- the proportion of individuals who discontinue and the reason for discontinuation.

Participant demographics and baseline characteristics such as temperature, age at randomisation, sex, area of residence, pre-existing antibodies to YF, reported history of YFV infection, and medical illness will be described both overall and separately for each vaccine dose groups (lower and full). Tests of statistical significance will not be undertaken for these demographic and baseline characteristics; rather the clinical importance of any imbalance will be noted.

### 5.3.2 Immunogenicity Analysis

All immunogenicity analyses will be pairwise comparisons of study arms (full vs lower dose group) within each cohort, and only a single lower dose vaccine group will be used for the sub-study in children.

#### *Primary Non-Inferiority Analysis*

The proportion of subjects who seroconvert will be presented by study arm for each study cohort, along with 95% confidence intervals. The primary analysis will be a pairwise statistical comparison of the rate of seroconversion at day 28 between full dose and each lower dose of vaccine using a non-inferiority test with a margin of non-inferiority of 10% in the PP population. Each immunogenicity assessment will be a pairwise comparison of the full dose and each lower dose within one study population (i.e. adults or children) using Dunnett's Test.

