### **Where is the study taking place, how many people does it involve and how are they selected?**

The vaccination study will take place in Kilifi, Kenya and Mbarara, Uganda among healthy adults and children who have previously not had the YF vaccine and/or YF infection and have no contraindications for vaccination. In total, 480 adults (240 at each site) and 420 children aged 9 to 12 months (210 at each site) will be included. To evaluate views and perceptions on the use of fractional YF vaccine doses we will approach and conduct discussions and interviews with various stakeholders in national vaccine policy in Kenya, Uganda, Senegal and other international institutions.

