**Table 5: Planned participant recruitment numbers in Kilifi and Mbarara**

| Population          | Allocation       | Participants in Kilifi (n) | Participants in Mbarara (n) | Total per allocation |
|---------------------|------------------|----------------------------|-----------------------------|----------------------|
| Adults
(N=480)   | Full dose        | 60                         | 60                          | 120           |
|                     | 1000 IU          | 60                         | 60                          | 120           |
|                     | 500 IU           | 60                         | 60                          | 120           |
|                     | 250 IU           | 60                         | 60                          | 120           |
| Children
(N=420) | Full dose        | 105                        | 105                         | 210           |
|                     | To be determined | 105                        | 105                         | 210           |

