likely to be substantially above the current minimum potency requirements, these data may not be scientifically explanatory regarding the minimum dose required for preventive use. Here, in this new complementary study, we aim to determine the lowest YF vaccine dose that is non-inferior to the current standard full dose among populations in sub-Saharan Africa (SSA). The study will be conducted in Kenya (KEMRI CGMRC, Kilifi) and Uganda (Epicentre, Mbarara) with trial participants recruited at both sites, using vaccine from one WHO-prequalified manufacturer (Institut Pasteur de Dakar, Senegal). Our primary aim is to compare the immunogenicity of full standard dose of vaccine with three lower doses in adults, using seroconversion at 28 days post-vaccination, measured by plaque reduction neutralization assay (PRNT50), as the endpoint. Adult participants (n=480) will be randomized for vaccination with full standard dose or with approximately 1000, 500 or 250 IU of vaccine (i.e. 4 arms, 1:1:1:1 allocation ratio). Safety and immunogenicity results will then be reviewed by the study Data and Safety Monitoring Board (DSMB), and the lowest non-inferior dose selected for assessment in a sub-study in children (n=420) in comparison to full standard dose (i.e. 2 arms, 1:1 allocation ratio) co-administered with the Expanded Program for Immunisation (EPI) Measles vaccine. Secondary objectives will include immunogenicity at 10 days, 1 year and 2 years post-vaccination, assessment of the influence of cross-reactive antibodies to other flaviviruses on vaccine immunogenicity, assessment of T and B cell immune responses, assessment of virologic and immunological kinetics and occurrence of serious adverse events (SAE). In addition, we will assess the range of views and perceptions of key stakeholders in vaccine policy and implementation on lower vaccine dose usage during YF epidemics and routine use. We expect the data from this qualitative study to inform the implementation of policies relating to low-dose vaccine usage for the control of YF and other diseases (e.g. pneumococcal vaccines) where such strategies are in consideration.

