### **3.2 Sample Size and Power Considerations**

This study will be powered to detect non-inferiority of each lower dose of vaccine (1000 IU, 500 IU, 250 IU) compared to the full standard vaccine dose.

For the adult study, assuming a 95% seroconversion rate, 90% power, 2.5% level of significance for a one-sided test and a non-inferiority margin of 10%, which gave a sample size of 100 per arm. The 10% non-inferiority margin was chosen in consideration of the public health consequence of a loss of protection but a potential increase in vaccine dosages in a situation where vaccine stocks are insufficient to respond to an outbreak. The sample size was increased by 20% to account for: i) losses to follow up and, ii) unevaluable participants with a positive serological response for YF virus at baseline. Thus, a total sample size of 480 will be required for the four vaccine dose groups (i.e. full dose, 1000 IU, 500 IU and 250 IU).

For the study in children, we assumed a 90% seroconversion rate (accounting for lower vaccine immunogenicity reported in children [4]), 90% power, 2.5% alpha for a one-sided test and a non-inferiority margin of 10%, which gave a sample size of 190 per arm. This was increased by 10% to account for 5% losses to follow up and 5% unevaluable participants with a positive serological response for YF virus at baseline. This gave a total sample size of 420 (i.e. 210 in the full dose group and 210 in the lower dose group).

Analyses of all other efficacy and safety endpoints are supporting only. Therefore, no significant adjustments will be made for multiple comparisons.

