#### *Pre-existing immunity interference*

We will perform a logistic regression to evaluate the impact of vaccine dose group and pre-existing immunity to YF on rate of seroconversion at Day 28. A logistic regression analysis will be conducted within each study cohort, with adjustment for age at randomization, site, sex, and baseline YF titre (as a continuous variable) and vaccine dose group as covariates. This analysis will be conducted in the subset of the ITT population which is seropositive to YF at baseline (ITT YF+) for each study cohort.

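### The primary seroconversion comparison names no site term although recruitment is planned equally by arm within two sites; stratifying by site is a small improvement at almost no cost

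*Supplement*

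**What the plan says.** SAP 5.3.2 (Primary Non-Inferiority Analysis) reads: "The primary analysis will be a pairwise statistical comparison of the rate of seroconversion at day 28 between full dose and each lower dose", against a 10% margin in the PP set. The same paragraph names Dunnett's test and confines each comparison to one study population, adults or children. Site is not mentioned.

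Table 5 of protocol v1.6, "Planned participant recruitment numbers in Kilifi and Mbarara", lists 60 adults per arm and 105 children per arm at each site. The lay summary agrees: "480 adults (240 at each site) and 420 children aged 9 to 12 months (210 at each site) will be included".

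Protocol 10.6 and SAP 3.3 describe a computer-generated schedule, scratch-card booklets and blocks sized to clinic days. Neither says that randomization is stratified by site.

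The SAP uses site in one analysis only, the logistic regression on pre-existing immunity, run "with adjustment for age at randomization, site, sex, and baseline YF titre" and dose group. That model is restricted to ITT participants who were seropositive at baseline. The PP definition in SAP 3.5 excludes them, so no planned PP analysis uses site. None of the seroconversion tables listed in SAP section 6.2 is by site.

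**The concern.** Equal planned numbers per arm within each site are most easily reached with separate allocation lists per site. The usual practice is then to carry site into the primary analysis. Leaving it out has two consequences if seroconversion differs between Kilifi and Mbarara.

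- The pooled binomial variance counts the between-site difference as noise, so the standard error is slightly too large.
- The PP set drops baseline seropositives, participants without a baseline or in-window Day 28 sample, and eligibility errors. If these exclusions fall unevenly by arm within site, part of the site difference enters the dose comparison.

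The 20% allowance in SAP 3.2 is not split by site or arm, so the plan does not address this. The comparison also guides which dose goes forward to children (SAP 3.4).

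**Working it through.** **Plan's own figures.** For adults the SAP gives "assuming a 95% seroconversion rate, 90% power" and "2.5% level of significance for a one-sided test and a non-inferiority margin of 10%, which gave a sample size of 100 per arm". With n = (1.960 + 1.282)² × 2p(1−p) / 0.10²:
- Adults, p = 0.95: 10.507 × 0.095 / 0.01 = 99.8, so 100.
- Children ("For the study in children, we assumed a 90% seroconversion rate"): 10.507 × 0.18 / 0.01 = 189.1, so 190.

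Both reproduce, without a site term.

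**Assumptions.** The documents give no seroconversion rates by site, so all site rates below are assumed.

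**Estimated variance with equal site numbers.** The share of the crude variance due to site is 1 − mean[p_s(1−p_s)] / [p̄(1−p̄)].
- 92% and 98%: 1 − 0.04660/0.04750 = 1.9%.
- 90% and 99%: 1 − 0.04995/0.05198 = 3.9%.

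**True variance with equal site numbers.** The crude and Mantel-Haenszel differences are then the same number, so their sampling SD is the same. At 99% and 91% with 50 per arm per site it is √(2 × 0.0459/100) = 3.03 points for both. The crude formula reports √(2 × 0.0475/100) = 3.08 points.

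**Bias from imbalance.** Bias = (difference between arms in site share) × (site gap in seroconversion).
- Extreme case, 55/45 v 45/55 with a 9-point gap: 0.10 × 0.09 = 0.9 points.
- Random loss in adults: 60 per site and arm with 1 in 6 lost (120 to 100 per arm). The variance of each retained count is 60 × (5/6) × (1/6) = 8.33. The SD of one arm's site share is about √16.67/200 = 2.04 points, and of the difference between two arms 2.04 × √2 = 2.9 points. The one-SD bias is 0.029 × 4 = 0.1 points at a 4-point gap and 0.029 × 9 = 0.26 points at a 9-point gap.
- In simulation, a difference in site share of 10 points or more arises in about 0.08% of pairwise comparisons. It is about 0.1% if losses are 5% at one site and 28% at the other, the same in every arm.
- Random loss in children, 105 per site and arm and 210 to 190 per arm: count variance 105 × (190/210) × (20/210) = 9.05; SD of the difference in share √18.1/380 × √2 = 1.6 points; bias at a 9-point gap 0.016 × 9 = 0.14 points.

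**Simulated operating characteristics.** 200,000 trials per scenario, 100 evaluable per arm, pooled Wald v Mantel-Haenszel by site with Sato variance. Type I error is at a true difference of −10 points in each site.

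| PP site split (full; lower) | Site rates | Quantity | Pooled | Stratified |
|---|---|---|---|---|
| 50/50; 50/50 | 95/95 | Power | 88.6% | 89.0% |
| 50/50; 50/50 | 99/91 | Power | 88.9% | 90.5% |
| 42/58; 58/42 | 95/95 | Power | 88.7% | 88.7% |
| 50/50; 50/50 | 99/91 | Type I error | 0.033 | 0.034 |
| 45/55; 55/45 | 97/93 | Type I error | 0.041 | 0.034 |
| 45/55; 55/45 | 99/91 | Type I error | 0.048 | 0.033 |

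The excess over 0.025 at balance comes from the Wald-type interval and is common to both methods. In the last two rows the pooled estimate is biased by 0.4 and 0.8 points; the stratified bias is within 0.02 points of zero.

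**The case against.** The strongest reply is that nothing in the plan is wrong here.

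- **Recruitment numbers.** Table 5 gives planned numbers, not fixed quotas, and site-stratified randomization is not stated. That sites are pooled is read from the SAP's silence. All of this stands.
- **Precision.** A reader might infer that stratifying makes the estimator itself more precise. Under balance it does not; only the estimated standard error shrinks. The unstratified analysis is then mildly conservative, which is the safe direction for a non-inferiority claim.
- **Bias.** A reader might also infer that the primary result will be materially biased. Bias needs both a site gap in seroconversion and losses that differ by arm within site. Baseline serostatus precedes allocation, and follow-up staff are blinded, so arm-related loss should be largely chance. Losses that differ by site but equally across arms cause no bias. The 0.9-point case is a tail event.
- **Cost.** Adding a stratified interval beside Dunnett's test would leave two methods for one primary analysis. The baseline-seropositive subset may be too small to stratify: the whole allowance is 20 per adult arm, or about 10 per arm per site, and it also covers losses to follow-up.

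These points limit the size and scope of the change. They do not remove the reason for it: the adjustment needs only a variable already recorded, and it protects against an imbalance that the plan does not otherwise handle.

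**Conclusion.** The point holds as a minor, optional improvement. The primary PP comparison has no site term although recruitment is planned equally by arm within site. The sample sizes are unaffected.

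The gain is 1.9% to 3.9% of the estimated variance at the assumed site rates, plus removal of a shift that is typically 0.1 to 0.3 points under random loss. Both vanish if the sites seroconvert alike, and stratifying then costs practically nothing: in simulation the SD rises only from 3.08 to 3.12 points even with a 42/58 v 58/42 split.

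The documents do not support calling the planned analysis invalid, or expecting a shift near 0.9 points. Nor would stratifying repair losses related to the outcome within a site. The simulations used a Wald-type stratified interval, so they show the direction and rough size of the effect, not the exact performance of the interval proposed below.

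**What to change.** Amend the primary analysis paragraph of SAP 5.3.2:

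- Specify the Day 28 risk difference for each lower dose v full dose stratified by site, with Mantel-Haenszel weights and a stratified Miettinen-Nurminen 95% confidence interval. Apply it to adults and children, in the PP and whole-ITT sets.
- State that this interval decides non-inferiority against the 10% margin, and whether it replaces the Dunnett's test named there or how the two are reconciled.
- Show the site-specific differences beside the stratified one.
- Leave the baseline-seropositive subset unstratified, or state a rule for sparse or empty strata.
- State in protocol 10.6 and SAP 3.3 whether randomization lists are prepared by site.

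The cost is a few sentences. Site is already known for every participant and already a covariate elsewhere in the SAP; no new data or larger sample is needed.

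### For the adult primary analysis the SAP names Dunnett's Test but also says no multiplicity adjustment is made; the two rules can disagree on the same data, and only the unadjusted one matches the sample size

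*Supplement*

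**What the plan says.** Four places in the SAP bear on the adult primary test.

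- **SAP 5.3.2, Primary Non-Inferiority Analysis.** Each lower dose is compared with the full dose "using a non-inferiority test with a margin of non-inferiority of 10% in the PP population". The next sentence describes a "pairwise comparison of the full dose and each lower dose within one study population (i.e. adults or children) using Dunnett's Test". It gives no level, sidedness or interval for Dunnett, and does not say how the test applies to a difference in proportions with a margin.
- **SAP 5.1.1**, on the same Day 28 comparison: "No adjustment for multiple comparisons will be made as only a single confidence interval will be constructed for each lower dose vaccine".
- **SAP 3.2.** The study is to be "powered to detect non-inferiority of each lower dose of vaccine (1000 IU, 500 IU, 250 IU) compared to the full standard vaccine dose", "assuming a 95% seroconversion rate, 90% power", at a "2.5% level of significance for a one-sided test and a non-inferiority margin of 10%, which gave a sample size of 100 per arm". Protocol 13.1 gives the same calculation.
- **SAP 5.3.** "All applicable statistical tests will be performed using a 5% significance level". Sidedness is not stated. The sentence after it sets all confidence intervals at 95%.

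Protocol 13.2.3 describes the pairwise non-inferiority comparison with a 10% margin and does not mention Dunnett. SAP 3.2 also has a sentence against multiplicity adjustment, but it concerns the other endpoints. The direct conflict is between SAP 5.3.2 and SAP 5.1.1.

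**The concern.** Dunnett's procedure exists to adjust for comparing several arms with one control, so an analysis cannot both use it and make no adjustment. Nothing in the SAP says which lower bound, the unadjusted one or the simultaneous one, must lie above -10 percentage points.

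The procedure is also built for normal means with a variance pooled over the arms. Seroconversion is binary and expected near 95%, so the arms' variances differ if their rates differ. A statistician following SAP 5.3.2 would have to improvise.

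This is the primary test, and under SAP 3.4 a dose must be shown non-inferior on seroconversion to be considered for the children's sub-study. If the rule is left open, the choice between two pass marks could be made after the results are known.

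**Working it through.** **Inputs.** 95% seroconversion in both arms, margin 0.10, one-sided 2.5%, 90% power, 100 evaluable per arm (SAP 3.2); three lower doses against one control, allocated 1:1:1:1 (SAP 1.2), which gives correlation 0.5 between the contrasts.

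**1. Reproduce the plan's figure.**
n = (1.960 + 1.282)² × 2 × 0.95 × 0.05 / 0.10² = 99.8, so 100 per arm. Adding 20% gives 120 per arm and 480 in total, as stated. This is the unadjusted one-sided 2.5% calculation.

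**2. Critical values.** Three contrasts, correlation 0.5, large-sample normal:

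| Rule | Critical value |
|---|---|
| Unadjusted, one-sided 2.5% | 1.960 |
| Dunnett, family-wise one-sided 2.5% | 2.349 (about 0.94% per comparison) |
| Dunnett, family-wise one-sided 5% | 2.062 |

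The SAP attaches no level to Dunnett, so both versions are shown.

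**3. Power per adult comparison, by the plan's formula.**
SE = √(0.095/100) = 0.0308; 0.10/SE = 3.244; power = Φ(3.244 − c).

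| Rule | Power at 100 per arm | Evaluable per arm for 90% |
|---|---|---|
| Unadjusted, c = 1.960 | Φ(1.284) = about 90% | 100 |
| Dunnett 2.5%, c = 2.349 | Φ(0.895) = 81.5% | 126 |
| Dunnett 5%, c = 2.062 | Φ(1.182) = 88.1% | 107 |

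If all 120 randomised per arm were evaluable, Dunnett at 2.5% would give 88.6%.

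**4. Can the rules disagree on one data set?** Full dose 98/100, lower dose 94/100, Wald interval:
SE = √(0.98×0.02/100 + 0.94×0.06/100) = 0.02757.
- Unadjusted: −0.04 − 1.960 × 0.02757 = −0.094, a pass.
- Dunnett 2.5%: −0.04 − 2.349 × 0.02757 = −0.105, a fail.

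With 96/100 against 93/100 the bounds are −9.3% and −10.6%. With a score statistic, the number a lower dose needs out of 100 rises by one person between 1.960 and 2.349 when the full dose has 95, 96, 98 or 99 of 100, and by two when it has 97 or 100.

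**5. Error rate if no adjustment is made.** With all three doses exactly 10 points below full dose, the chance that at least one passes at 1.960 is about 6.3% (trivariate normal).

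**6. Power depends on the interval method too.** By exact enumeration at 100 per arm and 95% in both arms, a score (Miettinen-Nurminen) interval has 83.2% power at 1.960 and 68.1% at 2.349. Any repair that names this method must therefore restate power.

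**7. Children.** SAP 5.3.2 uses a single lower dose there. With one contrast Dunnett's critical value is 1.960, the unadjusted value, and the stated 190 per arm reproduces: (1.960 + 1.282)² × 2 × 0.90 × 0.10 / 0.10² = 189.1, rounded up to 190.

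**The case against.** The strongest reply is that the intended rule can be recovered. SAP 3.2, SAP 5.1.1, protocol 13.1 and the 95% intervals in SAP 5.3 all fit one unadjusted interval per dose, and protocol 13.2.3 does not name Dunnett. On that reading the Dunnett phrase is a stray and 90% power stands by the plan's formula. Separate dose-against-control claims at a per-comparison level are also a defensible choice. Most of this is right and limits the point, but the phrase sits in the section that defines the primary test, and nothing overrides it.

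Stronger readings that a reader might infer are not supported:

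- **That the stated 90% power is simply wrong.** It falls short by the plan's formula only for adults and only if SAP 5.3.2 governs.
- **That SAP 5.3 adds a third, one-sided 5% level.** It gives no sidedness, and the lower limit of the 95% interval it prescribes is a one-sided 2.5% test. It needs clarifying, but it is not a clear conflict.
- **That the false-pass risk is 6.3% in general.** That figure needs all three doses exactly at the margin. With only 250 IU there, an unadjusted score test errs in about 2.1–2.3% of trials.
- **That this test alone selects the children's dose.** SAP 3.4 also weighs GMT, GMFI, the ITT results and safety, and protocol 8.1 involves the sponsor, manufacturer and stakeholders. Seroconversion non-inferiority is a necessary condition only.

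**Conclusion.** The concern holds for the adult primary analysis. The SAP gives two incompatible rules, and they can reverse the conclusion for a dose at seroconversion counts the trial could plausibly see. The cost depends on which governs:

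- **Dunnett governs:** power per comparison falls from 90% to about 81% at family-wise one-sided 2.5%, or about 88% at 5%.
- **SAP 5.1.1 governs:** power stays at 90% by the plan's formula, with a family-wise error of at most about 6.3% over the three doses.

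These figures assume 95% seroconversion in every arm (for power), 100 evaluable per arm, equal arm sizes and the large-sample normal approximation.

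**What to change.** Choose one rule and make the four SAP sections agree with it.

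1. **SAP 5.3.2:** delete the reference to Dunnett's Test. State, for example, that a lower dose is non-inferior if the lower limit of the two-sided 95% confidence interval (one-sided 2.5%) for lower-dose minus full-dose seroconversion lies above −10 percentage points, and name an interval method for a difference in proportions. This agrees with SAP 3.2 and 5.1.1.
2. **SAP 5.3:** say that the non-inferiority tests use this level.
3. **SAP 3.2:** restate adult power for the method named. At 100 evaluable per arm and 95% in both arms it is about 90% by the plan's formula and about 83% for a score interval.
4. **If the sponsor prefers a simultaneous adjustment:** remove the no-adjustment sentence from SAP 5.1.1, state the family-wise level, and restate power. At family-wise one-sided 2.5% it is about 81% by the plan's formula or about 68% with a score statistic.

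Testing the doses in a fixed order would control the family-wise error without adjusting the level. It is optional and a trade-off: with a score test and 95% in all arms, an order of 1000, 500, then 250 IU lowers the chance of a claim for 250 IU from 83% to 62%.

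The cost is SAP wording, settled before unblinding, with no new data. The price is a lower stated power if a score interval or a simultaneous adjustment is chosen.
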